### Blinding

The evaluator and the statistician are blinded to the intervention a participant accepts. Acupuncturists and patients are not blinded to the treatments they deliver because of the nature of the intervention.

### Intervention

There are four arms in this randomized controlled trial. The control group is supplied with standard antiemetic alone, and the other three arms consist of antiemetic drug and acupuncture.

#### Control groups

Participants in the control group received standard antiemetic alone. Standard antiemetic for all groups is based on the American Society of Clinical Oncology Clinical Practice Guideline [9]. 5-hydroxytryptamine-3 (5-HT3) antagonist (Ramosetron, Tropisetron) and dexamethasone will be administered before the chemotherapy treatment.

#### Acupuncture groups

Three acupuncture groups will receive electro-acupuncture with different acupoint combinations: Acupuncture group I and II will receive distal-proximal point association, and Acupuncture group III will receive local distribution point association. The acupuncturists are the members who hold a Chinese medicine practitioner license from the Ministry of Health of the People’s Republic of China.

##### Acupuncture group I: acupoints “PC6+ CV12” plus antiemetic drug

Participants in Acupuncture group I will receive electro-acupuncture at the Neiguan (PC6) point and Zhongwan (CV12) point. The location of Neiguan (PC6) is on the anterior aspect of the forearm, between the tendons of the palmaris longus and the flexor carpi radialis, 2 B-cun proximal to the palmar wrist crease [10]. The location of Zhongwan (CV12) is on the upper abdomen, 4 B-cun superior to the center of the umbilicus, on the anterior median line [10].

##### Acupuncture group II: acupoints “ST36+ CV12” plus antiemetic drug

Participants in Acupuncture group II will receive electroacupunture at Zusanli (ST36) and Zhongwan (CV12) points. The location of Zusanli (ST36) is on anterior aspect of the leg, on the line connecting ST35 with ST41, 3 B-cun inferior to ST35 [10]. The location of Zhongwan (CV12) has been introduced above.

##### Acupuncture group III: acupoints “CV12+ CV13” plus antiemetic drug

Participants in Acupuncture group III will receive electroacupuncture at Zhongwan (CV12) point and Shangwan (CV13) points. The location of Shangwan (CV13) is on the upper abdomen, 5 B-cun superior to the center of the umbilicus, on the anterior median line [10]. The location of Zhongwan (CV12) has been introduced above.

Disposable, stainless steel acupuncture needles will be used in this trial. The acupuncturists will first insert needles into the acupoints, then the needles will be manipulated until“de qi”sensation is achieved. Next, the needle will be connected to an electroacupuncture apparatus. The positive pole is linked to the needle, and the reference pole is secured approximately one cm in the proximity of the acupoint with a plaster. The electro-acupuncture treatment will use a frequency of 2/10 Hz, and the intensity of stimulation will be adjusted according to the patient’s tolerance. The electric current will be set at less than 10 mA. The procedure will last for 30 min. Treatment is scheduled to occur 30–60 min before chemotherapy infusion and will last for 4 days. Detailed information on acupuncture treatment is summarized based on the revised STRICTA recommendations [11] in Table 1.

**Table 1 Tab1:** Acupuncture treatment details based on the STRICTA checklist [11]

Item	Detail
1.Acupuncture rationale	1a) Style of acupuncture
	- electro-acupuncture
	1b) Reasoning for treatment provided, based on historical context, literature sources, and/or consensus methods, with references where appropriate
	- electro-acupuncture treatment based on the theory of TCM, literature sources, and clinical experience in acupuncture and CINV, such as references [16] and [17].
	1c) Extent to which treatment was varied
	- The treatment was not varied.
2. Details of needling	2a) Number of needle insertions per subject per session (mean and range where relevant)
	- From 2 to 3.
	2b) Names (or location if no standard name) of points used (uni/bilateral)
	- Four points used: ST36 (bilateral); PC6 (bilateral) ;CV12(unilateral); CV13 (unilateral).
	2c) Depth of insertion, based on a specified unit of measurement, or on a particular tissue level
	- PC6: 0.5 body-inches; ST36: 1-1.5 body-inches; CV12 and CV13: 1-1.5 body-inches.
	2d) Response sought (e.g., de qi or muscle twitch response)
	- ‘De qi’ sensation will be achieved by lifting and thrusting combined with twirling and rotating the needles.
	2e) Needle stimulation (e.g., manual, electrical)
	- Electrical stimulation: the frequency is 2/10 Hz, and the intensity of stimulation is adjusted according to the patient’s tolerance (maximum of 10 mA).
	2f) Needle retention time
	- Thirty minutes
	2g) Needle type (diameter, length, and manufacturer or material)
	- A disposable stainless steel acupuncture needle, 0.25mm × 40 mm (Huatuo, Suzhou Medical Co. Ltd., Jiangsu, China).
3.Treatment regimen	3a) Number of treatment sessions
	- Four treatment sessions in acupuncture groups.
	3b) Frequency and duration of treatment sessions
	- Once daily for 4 days, 30 minutes for each session.
4. Other components of treatment	4a) Details of other interventions administered to the acupuncture group (e.g., moxibustion, cupping, herbs, exercises, lifestyle advice)
	- No other interventions.
	4b) Setting and context of treatment, including instructions to practitioners, and information and explanations to patients
	- University hospitals. - Participants will be informed about acupuncture treatment in the study as follows: “In this study, eletroacupuncture for CINV will be used based on traditional Chinese medicine.”
5.Practitioner background	5) Description of participating acupuncturists (qualification or professional affiliation, years in acupuncture practice, other relevant experience)
	- The participating acupuncturists have all majored in acupuncture, have an acupuncture degree, and are qualified doctors of Tradition Chinese Medicine. All have at least 3 years of experience, and will have been trained in the standard operating procedure of electro-acupuncture on CINV. Thus, they are able to provide identical acupuncture treatment in accordance with a pre-defined protocol.
6. Control or comparator interventions	6a) Rationale for the control or comparator in the context of the research question, with sources that justify this choice
	- The control group is supplied with standard antiemetic alone, so as to provide patients with conventional treatment for CINV.
	6b) Precise description of the control or comparator. If sham acupuncture or any other type of acupuncture-like control is used, provide details as for items 1 to 3 above.
	- Participants in the control group will not receive acupuncture treatment.

### Participant timeline

Enrollment will be conducted the day before chemotherapy (day 0). The electro -acupuncture intervention will be given once daily from day 1 to day 4. The schedule of enrollment, interventions, and assessments is shown in Table 2.

**Table 2 Tab2:** The schedule of enrollment, interventions, and assessments

	Study period								
	Enrolment	Allocation	Post-allocation						Close-out
Time points	-t1	t0	t1	t2	t3	t4	t5	t6-t20	t21
Enrollment									
Eligibility screen	√								
Informed consent	√								
Allocation		√							
Interventions									
Control group									
Experimental group I			√	√	√	√			
Experimental group II			√	√	√	√			
Experimental group III			√	√	√	√			
Assessments									
Baseline variables	√	√							
The frequency of nausea and vomiting		√	√	√	√	√	√	√	√
The grading of nausea and vomiting		√	√	√	√	√	√	√	√
Rhodes Index of nausea, vomiting and retching		√	√	√	√	√	√	√	√
The grading of constipation and diarrhea		√					√		√
eletrogastrogram		√					√		√
quality of life		√					√		√
anxiety and depression		√					√		√
Other adverse effect during the chemotherapy							√		√
The adverse effects of acupuncture			√	√	√	√			

t0, the day before chemotherapy; t1-t5, the first day to the fifth day of chemotherapy; t6-t21, the sixth day to the 21st day of chemotherapy

### Outcome measures

The observation period will cover the day before chemotherapy (day 0) to the fifth day of chemotherapy (day 5). Follow-ups will be conducted from the sixth day (day 6) to the twenty first day (day 21) of chemotherapy. Participants will be asked to keep CINV diaries from the sixth day (day 6) to the twentieth day of chemotherapy (day 20).

#### Primary outcome measures

The primary outcome measures are as follows:Frequency of nausea and vomiting: total nausea and vomiting episodes per person over the 6-day study period will be recorded. The frequency of nausea and vomiting is the most valuable measurement for evaluation.Grading of nausea and vomiting: nausea and vomiting will be graded by Common Terminology Criteria for Adverse Events Version 4.0 [12].Rhodes Index of Nausea, Vomiting and Retching: nausea, vomiting and retching will be measured as separate entities by Rhodes Index of Nausea, Vomiting and Retching, which have 8 items with 5-point Likert scales. The frequency and distress of all entities are measured, as well as the duration of nausea and the amount of vomitius. [13]

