### Inclusion and exclusion criteria

#### Inclusion criteria

Participants who meet all of the following criteria will be considered for enrollment. The inclusion criteria are as follows: (1) Diagnosed with cancer and need chemotherapy. (2) The score of Karnofsky (KPS) ≥ 70. (3) Between 18 and 80 years old (either sex). (4) Receiving chemotherapy as outpatients or inpatients. (5) Receiving chemotherapy for one or multiple cycles, but the patient will be taken into the study only once. (6) Patients receiving chemotherapy containing cis-platinum (cis-platinum ≥ 75 mg/m^2^) or antharcycline-combined chemotherapy (doxorubicin ≥ 40 mg/m^2^ or epirubicin ≥ 60 mg/m^2^). (7) Life expectancy ≥ 6 months. (8) Willing to participate in the study and be randomly allocated into one of the four study groups.

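### As its six-day window reads, the primary episode count includes the day before chemotherapy and acupuncture, which adds variance and shrinks relative and standardised differences by an unknown, possibly small, amount

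*Protocol article*

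**What the plan says.** All references are to the protocol article.

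- **Primary outcome measures** describes the frequency outcome as a total: "total nausea and vomiting episodes per person over the 6-day study period will be recorded". It ranks this outcome first: "The frequency of nausea and vomiting is the most valuable measurement for evaluation". The sentence does not name the six days.
- **Outcome measures** gives the dates: "The observation period will cover the day before chemotherapy (day 0) to the fifth day of chemotherapy (day 5").
- **Participant timeline** places enrolment on day 0 and states that the "intervention will be given once daily from day 1 to day 4". The footnote to Table 2 reads "t0, the day before chemotherapy; t1-t5, the first day to the fifth day of chemotherapy", and the table schedules the frequency of nausea and vomiting at t0 as well as at t1 to t5.
- **Acupuncture group III**, in the paragraph on the procedure, times the sessions: "Treatment is scheduled to occur 30–60 min before chemotherapy infusion and will last for 4 days".
- **Inclusion criteria**, item 5, admits patients beyond their first cycle: "Receiving chemotherapy for one or multiple cycles, but the patient will be taken into the study only once".

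**The concern.** Recording symptoms on the day before chemotherapy is sound as a baseline. Adding them to the outcome total is a different matter. Whatever happens on day 0 cannot be caused by the cycle under study and cannot be changed by needling that starts on day 1. Day 0 can therefore add noise to the total but no information about the treatment effect.

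Day-0 counts cannot be taken as zero. The exclusion criteria remove nausea and vomiting due to opioids, metabolic imbalance and mechanical causes, but not symptoms left over from, or anticipating, chemotherapy in a patient already treated. At stake are some power and the size of any relative effect, on the outcome that the protocol values most.

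**Working it through.** **1. Which six days.** Day 0 to day 5 is 6 days; day 1 to day 5 is 5 days. The article sets out no other six-day window, and nothing in it takes day 0 out of the total. This is an inference from two sections, but it is the only reading that fits the number six.

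**2. The plan's own figure.** Sample size calculation gives 192 patients and 20% drop-out: 192 / (1 − 0.20) = 240, or 60 per arm, which reproduces. Evaluable patients per arm: 192 / 4 = 48. The 192 itself cannot be reproduced, because the article gives no mean, SD or rate.

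**3. Absolute difference.** Suppose the means over days 1–5 are 10 and 6, and each arm has a mean of 1 on day 0. The totals are 11 and 7. The difference is 4 either way, but the ratio moves from 0.60 to 7/11 = 0.64.

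**4. Relative difference.** Let m0 be the day-0 rate as a fraction of the comparator's daily rate on days 1–5 (assumed), with a true ratio of 0.70. The observed ratio is (m0 + 5 × 0.70) / (m0 + 5).

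| m0 | Observed ratio | A true 30% reduction reads as |
|---|---|---|
| 0 | 3.50/5.00 = 0.700 | 30.0% |
| 0.25 | 3.75/5.25 = 0.714 | 28.6% |
| 0.50 | 4.00/5.50 = 0.727 | 27.3% |
| 1.00 | 4.50/6.00 = 0.750 | 25.0% |

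**5. Power for a pairwise comparison of means.** Take the planned 90% power at 5% (two-sided assumed) with 48 per arm as holding for the days 1–5 count. The detectable standardised difference is (1.960 + 1.282) × √(2/48) = 0.662. Let k be the day-0 SD divided by the SD of the days 1–5 total, and ρ their correlation (both assumed). Including day 0 multiplies the SD by √(1 + k² + 2ρk).

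| k | Power, ρ = 0 | Power, ρ = 0.5 |
|---|---|---|
| 0 | 90.0% | 90.0% |
| 0.1 | 89.7% | 86.8% |
| 0.2 | 88.9% | 82.9% |
| 0.3 | 87.4% | 78.5% |
| 0.45 | 84.1% | 71.4% |

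For example, k = 0.2 and ρ = 0.5 give a multiplier of √1.24 = 1.114 and a standardised difference of 0.662 / 1.114 = 0.594. The last row is an upper case: k = 1/√5 means that day 0 varies as much as an average chemotherapy day, if days are independent.

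**6. Rank test.** Overdispersed counts were simulated (1.5 episodes per day, dispersion 1, rate ratio 0.6, 48 per arm, Mann-Whitney, 4,000 replicates). Power without day 0 was about 0.50, so these figures show the direction and spread of the loss and are not the trial's planned power. At m0 = 0.5 the loss was about 2 points if day 0 was independent of later days, and 8 to 9 points if one patient susceptibility drove both. At m0 = 1 the losses were 3 to 6 points and about 14 points. At m0 = 0.1 the loss was 0 to 2 points under either assumption.

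**The case against.** The strongest case on the other side concerns the consequence, not the window.

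- A reader might infer that day 0 shrinks every between-arm difference, or biases the comparison. Neither follows. Day 0 precedes treatment, so under randomisation it contributes equally to each arm in expectation. The absolute mean difference is unbiased and the type I error holds. A chance imbalance on day 0 is random error. The attenuation applies to ratios, standardised differences and power, and the Statistical analysis section names no rate ratio as its effect measure.
- A reader might infer that all the primary outcomes are affected. Only the frequency outcome is described as a total. The CTCAE grades and the Rhodes Index are scheduled by day, and the article does not say that they are summed.
- A reader might infer that the same values serve as both baseline and outcome in one analysis. Table 2 collects them at t0, but no change-from-baseline or baseline-adjusted analysis of the count is stated.
- The planned repeated measures analysis keeps the days apart and can treat day 0 as a pre-treatment time point. Covariates may also be set in an analysis plan that is not shown, so their absence here is no finding.
- The size is soft. Highly emetogenic regimens and the listed exclusions may leave most day-0 counts at or near zero, and a day-0 rate equal to the average of days 1–5 is extreme.

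All of this stands, and it limits the point. It does not remove it. The article states a six-day total, and an analysis plan that followed it would carry the extra day forward.

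**Conclusion.** The point holds for the episode total, as something the sponsor should fix rather than a threat to the trial's validity. Confidence is high that the window as written includes day 0, and low on how much that costs. A working range is a true 30% reduction read as 28.6% to 25.0%, and planned power of 90% falling to about 89% to 83% at k = 0.2. Both rest on assumed day-0 rates, SDs and correlations, since the article supplies none. The loss is nil if every day-0 count is zero. The eligibility of patients from earlier cycles means that this cannot be relied on.

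**What to change.** Define the primary count as episodes on days 1–5 (t1–t5), and use the day-0 count only as a baseline covariate. The Kruskal-Wallis test takes no covariate, so where that test is used day 0 would simply be left out of the total and reported as baseline.

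The cost is one sentence in the outcome definition. Table 2 already schedules the frequency by day, so no data, visits or patients are added, and the 240 stands. Because recruitment is under way, the change should be dated and made before unblinding; choosing between five and six days once results are known would be a post-hoc choice on the leading primary outcome. The six-day total can be kept as a supporting analysis for continuity with the published definition.

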#### Secondary outcome measures

Secondary outcome measures include the following:Grading of constipation and diarrhea: constipation and diarrhea will be evaluated by Common Terminology Criteria for Adverse Events Version 4.0 [12].Electrogastrogram: gastrointestinal motility will be monitored by electrogastrogram.Assessment of quality of life: the Functional Assessment of Cancer Therapy- General (FACT-G) [14] will be applied to assess four domains of patient quality of life, including physical, social/family, emotional, and functional well-being.Assessment of anxiety and depression: the Hospital Anxiety and Depression Scale [15] will be used to assess anxiety with seven items and depression with another seven items.Other adverse effects, including appetite, will be assessed by Common Terminology Criteria for Adverse Events Version 4.0 [12].

### Sample size calculation

A sample size calculation was performed based on the result of a trial by Shen J [8] and the results of a pilot study. To detect a significant difference between any two groups with a power of 90 % and type I error of 5 %, the calculated number of patients is 192. Considering a 20 % drop-out rate, the total sample size needs 240 patients and 60 patients in each group.

### Statistical analysis

Statistical analysis will also be performed by the Clinical Evaluation Center at China Academy of Chinese Medical Science. The statistician is blinded from the allocation of groups. The Kruskal-Wallis test will be employed in the analysis of skewed distribution data. Chi-square analysis will be used for categorical variables, and Analysis of variance (ANOVA) for numerical variables. Repeated measures analysis will be used in the different time point assessment. A *P* value less than 0.05 is regarded as statistically significant.

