## Background

Chemotherapy-induced nausea and vomiting (CINV) are common side-effects of many antineoplastic regimens and can occur for several days after treatment [1]. CINV significantly impacts the patient’ quality of life and nutritional status, and may lead to dose reduction or treatment discontinuation, subsequently increasing the risk of disease progression [2]. Although effective guidelines for CINV prevention exist for both moderately and highly emetogenic chemotherapies, adherence to these guidelines is not widely practiced because of their expensive costs and side-effects, such as headaches, dizziness, constipation, and insomnia [1].

Acupuncture treatment is one of the most sought-after therapeutic modalities in complementary and alternative medicine [3]. It is a safe medical procedure with minimal side effects. Evidence for the therapeutic effects of acupuncture on CINV exists [4]. Electroacupuncture for CINV management has been recommended by the American Society of Clinical Oncology [5]. Based on Traditional Chinese Medicine (TCM), the combination of acupoints can strengthen the essential and comprehensive therapeutic effects of acupuncture [6]. However, no consensus currently exists on the optimal acupoint combination for controlling CINV. For example, Gottschling S [7] found that stimulating PC6 (Neiguan), CV12 (Zhongwan), ST36 (Zusanli) and LI4 (Hegu) may effectively prevent CINV; Shen J [8] concluded that electro-acupuncture on PC6 (Neiguan) and ST36 (Zusanli) is more effective in controlling emesis than antiemetic pharmacotherapy alone. Therefore, we propose a randomized, controlled trial to determine the optimal combination of acupoints for CINV management.

In this trial, we aim to determine whether different acupoint combinations similarly manage CINV. We also aim to determine whether distal-proximal point association or local distribution point association more efficiently manages CINV.

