### Hypothesis

According to the theory of TCM, the combination of acupoints can achieve a synergistic effect. In addition, distal-proximal point association and local distribution point association are the classic methods for combinating acupoints. We hypothesize that distal-proximal point association will achieve better therapeutic effect by reducing toxicity and enhance efficacy in CINV management.

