### Design

This is a four-armed parallel randomized controlled trial (RCT). 240 participants will be randomly assigned to four groups (a control group and three acupuncture groups) through central randomization in a 1:1:1:1 ratio. The flow chart is shown in Fig. 1.

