## Discussion

This study protocol expands current literature regarding the efficacy of acupuncture on CINV. Previous reviews showed that acupoint stimulation has a certain effect on CINV. However, the effects of different acupoint combinations are inconsistent. We designed our trial to compare the effects of distal-proximal point association and local distribution point association.

More than 300 acupuncture points are located on the body and each point has its own therapeutic indication. The correct selection and combination of acupoints are the keys to the curative effects of acupuncture [6]. Before developing the trial protocol, we screened a range of published articles and ancient books. Our literature search showed that PC6, ST36, and CV12 are the most commonly used acupoints for managing CINV [16, 17]. We selected PC6 and ST36 as the distal acupoints, and CV12 as the local acupoint. Based on the theory of Chinese acupuncture, distal-proximal acupoint association and local distribution point association are the two classic methods for combining acupoints. Distal-proximal acupoint association is also the most commonly used method in clinical applications. In this trial, there are three different acupuncture groups: “PC6 and CV12” and “ST36 and CV12” are the two disal-proximal acupoint association groups, and “CV12 and CV13” is the local distribution point association group. Therefore, we expect that distal-proximal point association (“PC6 and CV12” or “ST36 and CV12”) will have better effect than local distribution point association (“CV12 and CV13”). Furthermore, we can screen the most effective acupoint combination for clinical application from these three groups.

Although the manipulators and participants cannot be blinded to the group allocation in this study, all outcome measures will be administered and collected by a blinded estimator, and statisticians blinded to group assignment will perform data analysis. With respect to clinical quality control, the manipulators, estimators and statisticians will work independently to reduce the adverse impacts of artificial factors on data. A third party has been invited to manage data independently and to design a central randomization system for minimizing bias and enhancing clinical research quality.

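### The analysis section names only tests of equality across arms; none estimates the distal-proximal versus local comparison that the trial hypothesises

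*Protocol article*

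**What the plan says.** The protocol article states its question several times, and in one direction. Background: the trial is to "determine whether distal-proximal point association or local distribution point association more efficiently manages CINV". Hypothesis: "We hypothesize that distal-proximal point association will achieve better therapeutic effect". Discussion: either distal-proximal pair "will have better effect than local distribution point association". Groups I (PC6 + CV12) and II (ST36 + CV12) are distal-proximal, and group III (CV12 + CV13) is local. The fourth arm is antiemetic alone. Allocation is "through central randomization in a 1:1:1:1 ratio".

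The Statistical analysis section assigns one method to each type of data: "The Kruskal-Wallis test will be employed in the analysis of skewed distribution data", chi-square for categorical variables, ANOVA for numerical ones, and repeated measures analysis across time points. The significance level is 0.05. It names no contrast, pairwise comparison, direction or pooling of arms.

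The Sample size calculation section aims at a difference between any pair of arms with 90% power and 5% type I error. It arrives at 192 patients, raised to 240 for 20% drop-out. It states no effect size or standard deviation.

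On blinding: "Acupuncturists and patients are not blinded to the treatments they deliver". The evaluator and statistician are blinded, and control patients receive no acupuncture of any kind.

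**The concern.** Three parts of the document point at three targets. The hypothesis concerns I and II against III, the sample size concerns any pair of arms, and the named tests, on the natural reading of a four-arm trial, concern equality of all arms.

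An omnibus test becomes significant when any arm departs from the others, in either direction. Here the arm most likely to depart is control, which differs from the other three in whether needling is given at all, while the three acupuncture arms differ only in which points are used. If the omnibus P value were taken as the answer, a difference between control and acupuncture in general could be reported as support for distal-proximal association.

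**Working it through.** **The plan's own figure.** 192 / (1 − 0.20) = 240, or 60 per arm, with 192 / 4 = 48 evaluable per arm. This reproduces. The 192 cannot be rebuilt because no effect size is given. Working backwards for one two-sided pairwise comparison at 5% and 90% power: d = (1.960 + 1.282) × √(2/48) = 0.66 SD. That is an assumption about what the authors had in mind, so a range is used below.

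**Omnibus test when distal-proximal equals local.** Let control have mean 0 and all three acupuncture arms be better by d (in SD units). The grand mean is 0.75d, the sum of squared deviations is 0.75d², and the noncentrality is λ = 48 × 0.75 × d² = 36d². Power is the probability that a noncentral F(3, 188, λ) exceeds the 5% critical value of 2.65.

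| Assumed shift d | λ | ANOVA significant | Distal-versus-local contrast significant |
|---|---|---|---|
| 0.33 | 3.9 | 35% | 5% |
| 0.5 | 9.0 | 70% | 5% |
| 0.67 | 16.2 | 93% | 5% |
| 0.8 | 23.0 | 99% | 5% |

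The last column is the nominal error rate, because the contrast does not involve the control arm.

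**Omnibus test when the hypothesis is reversed.** With local better by 0.66 SD and distal-proximal equal to control, one arm again differs from three others, λ = 36 × 0.66² = 15.7, and the ANOVA is significant 92% of the time.

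**Kruskal-Wallis.** Simulation with 48 per arm (5,000 runs), again with identical acupuncture arms:
- normal data, control worse by 0.66 SD: Kruskal-Wallis significant 90% of the time;
- skewed counts (assumed negative binomial), control mean 6 against 3: 90%;
- the same with 6 against 4: 47%.

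A rank test of I and II pooled against III was significant about 5% of the time in each case.

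**What a targeted comparison offers.** Assume a distal-local gap of 0.5 SD, I and II equal in effect, and 188 error degrees of freedom (critical t 1.973):
- mean(I, II) minus III: SE = √(1/96 + 1/48) = 0.177; 0.5 / 0.177 = 2.83; power 80%.
- One pair, such as I minus III: SE = √(2/48) = 0.204; 0.5 / 0.204 = 2.45; power 68%.
- One pair tested at 0.025 (Bonferroni for two; critical t 2.26): power 58%.

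If only I works (I better by 0.5 SD, II equal to III), the pooled difference halves to 0.25 SD; 0.25 / 0.177 = 1.41; contrast power 29%.

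**The case against.** The strongest reply is that this is an article-length summary. It gives a test family per data type and does not say that the omnibus P value is the primary inference. Sizing the trial for any pair of arms shows that pairwise comparisons were intended, and follow-up procedures may sit in a full protocol or analysis plan that is not shown. This stands against the inference that the trial cannot test its hypothesis or never meant to; the document does not support that reading. Nor are the named tests invalid: they answer whether any arm differs. What remains is that the analysis, followed as written, yields a significance call on a question other than the stated one.

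A second reply is that the hypothesis is not the only aim. The Background also asks whether the combinations perform similarly, the Objectives cover the efficacy and safety of both associations, and the Discussion hopes to pick the best of the three. The Discussion joins the two distal-proximal pairs with an *or*, so averaging I and II is one faithful reading and not the only one. This stands, and the fix leaves the choice open.

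A reader might also infer that the lack of a sham arm is an error, or that the Discussion's statement that "all outcome measures will be administered and collected by a blinded estimator" claims to protect patient-reported nausea from expectation. Neither follows. The article openly says that patients are not blinded, in all arms and not just control, and justifies control as conventional treatment. The Discussion sentence opens by conceding the limit and does not make that claim. The relevance here is narrower: an add-on difference in unblinded patients can include expectation and attention, so it should not settle the distal-versus-local question.

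**Conclusion.** The point holds as a mismatch between the stated hypothesis and the named analysis. On the tests as named, a significant result does not show whether distal-proximal differs from local, or in which direction.

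The size depends on how far control differs from acupuncture, which the document does not say. Over assumed shifts of 0.33 to 0.8 SD, the chance of a significant ANOVA with no distal-local difference runs from 35% to 99%. It would be wrong to read any one of these figures as the trial's own error rate. They assume 48 evaluable patients per arm, two-sided 5% testing, tests run over all four arms and, for the ANOVA figures, normal data with equal variances. The simulated counts point the same way.

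**What to change.** Before unblinded analysis, add to the Statistical analysis section a pre-specified comparison of groups I and II with group III. Apply it to the primary count (total nausea and vomiting episodes per person over the six-day period), with a 95% confidence interval and a method suited to skewed counts. Two forms are acceptable:

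- the planned contrast mean(I, II) minus III as the main comparison, followed by I versus III and II versus III; or
- those two pairwise comparisons as the main tests, with multiplicity control.

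Report each acupuncture arm against control separately, labelled as an add-on effect in unblinded patients. State that the omnibus P value is not the answer to the hypothesis.

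The cost is wording only; no patients or data are added. Pooling has more power if I and II work equally well but can mask a difference between them, which reporting both pairs covers. The pairwise form avoids the masking at some loss of power. The choice should be recorded before anyone sees results by arm, since a contrast chosen afterwards would be data-driven.
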